### Randomization

After selecting the participants according to the inclusion and exclusion criteria, baseline assessments will be performed. The participants will then be randomized into control or intervention groups. A random sequence will be determined from the randomization website (http://www.jerrydallal.com/random/permute.htm) in blocks of four. Randomization will be performed by a technician who is blind to the title of each group. In order to protect confidentiality in all stages of the trial, each participant will be assigned a unique identification code.

### Recruitment and consent

Chemical warfare victims residing in Tehran and its suburbs will be identified from the administrative database for this condition. Those with a history of exposure to mustard gas will be invited to participate in the study. The patients will undergo specialized examinations and baseline assessments. Patients with the inclusion criteria will read the informed consent form (Additional file 3), previously provided by study supervisor, and receive further explanation in the case of any confusion regarding the contents. If the patient needs more time to think or to consult their family members they will be given a week to decide.

During the study, the patient will be excluded from the study if any of the following occurs: any of the exclusion criteria emerge in the patient; the patient is affected with any disease or medical condition that will make it difficult for them to continue participating in the study; the patient wishes to withdraw from the study for personal reasons; emigration; or death. Compliance with PR is defined as missing fewer than four sessions and a per-protocol analysis as well as intention to treat will be carried out. During the trial, patients can receive their care but they will not be allowed to undergo any interventional study.

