**Methods:**

We outline the protocol for an assessor-blind, two-armed, parallel-design randomized controlled clinical trial (IRCT2016051127848N1). Sixty patients with respiratory disease due to documented sulfur mustard gas exposure will be randomized to either take part in a 6-week pulmonary rehabilitation programme or receive usual care. Inclusion criteria include forced expiratory volume in 1 second < 80% predicted and Medical Research Council dyspnoea score ≥ 3. The primary endpoint will be the change in cycle endurance time at 70% baseline exercise capacity at 6 weeks. Lung function, physical activity, the strength and endurance of the quadriceps muscle, and quality of life will also be compared. Outcomes will be assessed at 6 weeks and 12 months. Health care utilization will also be assessed.

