### Participants

The participants are chemical warfare victims with contemporaneously documented exposure to mustard gas, residing in Tehran and its suburbs, who have symptomatic lung disease. Inclusion criteria include FEV_1_ < 80% and MRC dyspnoea score ≥ 3 [28].

Exclusion criteria are: any type of debilitating clinical condition that prevents the patient from participating in the rehabilitation programme, such as arthritis; any type of clinical condition that will endanger the patient during the physical exercises, such as uncontrolled cardiac diseases; the presence of other non-chemical-related pulmonary diseases, like asthma; active malignancy; and severe cognitive disorder and psychiatric disease that is associated with memory disorder.

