### Sample size and statistical analysis

Assuming a 105-s improvement in the time limit in the treatment arm and a 20-s improvement in controls with an SD of 100, 90% power and a significance level of 5% requires 60 patients to complete the study.

The data will be cleaned and assessed for outliers and missing variables. Outcomes will be compared using ANOVA adjusted for baseline parameters. The data will be analysed by *t* test, chi-square test and, if required, non-parametric tests and with Excel 2010 and SPSS Statistics 20 software at a level of significance of 0.05.

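### Removing randomised patients from the study when new illness or an exclusion criterion emerges contradicts the promised intention-to-treat analysis and risks a bias in favour of rehabilitation

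*Protocol article*

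**What the plan says.** All references are to the protocol article.

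- **Rule on leaving the study (Recruitment and consent).** The rule applies after randomisation and reads: "the patient will be excluded from the study if any of the following occurs: any of the exclusion criteria emerge in the patient". A second trigger is that "the patient is affected with any disease or medical condition that will make it difficult for them to continue participating in the study". The other three are personal withdrawal, emigration and death.
- **Analysis sets (same paragraph, next sentence).** Compliance is defined by the number of missed sessions, and "a per-protocol analysis as well as intention to treat will be carried out".
- **Exclusion criteria (Participants).** One is "any type of debilitating clinical condition that prevents the patient from participating in the rehabilitation programme, such as arthritis". Another covers conditions that would put the patient at risk while exercising. The rest concern other lung disease, malignancy, and cognitive or psychiatric disease.
- **Contact with patients.** Usual care and Follow-up give both arms 12 monthly visits. The Discussion describes rehabilitation three times a week for 6 weeks.
- **Timing.** The primary outcome, cycle endurance time, is taken at 6 weeks, and outcomes are measured again at 12 months. Under Trial status, enrolment ended in August 2018 and the last visit is due in August 2019.

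**The concern.** Intention to treat means that every randomised patient is analysed in the allocated arm, with outcomes sought from all of them. A rule that takes randomised patients out of the study because their health has changed works against this. The article does not distinguish a patient who stops the sessions from one who leaves the trial, and no section says that an excluded patient is still tested or kept in the analysis.

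The loss may also differ by arm. Two of the exclusion criteria refer to the programme or the exercises, and rehabilitation patients are seen far more often during the 6 weeks that lead to the primary endpoint. The same new joint or heart problem is more likely to be noticed, and to count as a reason for exclusion, in a patient attending sessions. The article blinds the outcome assessors, but does not say that whoever judges continuation to be difficult is blinded.

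If patients who do badly leave the rehabilitation arm more often than the control arm, the remaining comparison favours rehabilitation. Exacerbations and hospitalisations are also outcomes, so a patient excluded for serious illness may leave before later events are counted.

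**Working it through.** **1. The two statements side by side.** The exclusion rule acts after randomisation, is triggered by health, and ends participation in the study. The analysis sentence promises a comparison of everyone as randomised. Followed literally, the first stops collecting outcomes that the second needs. An analysis plan can choose a method for missing data, but it cannot recover assessments that were never made.

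**2. The plan's own sample size.** Inputs from Sample size and statistical analysis: the means are given as "Assuming a 105-s improvement in the time limit in the treatment arm and a 20-s improvement in controls"; the spread is stated next, "with an SD of 100"; and the resulting requirement is that "90% power and a significance level of 5% requires 60 patients to complete the study".

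- Difference: 105 − 20 = 85 s.
- Per arm, two-sided 5%, 90% power: 2 × (1.960 + 1.282)² × 100² / 85² = 29.1, rounded up to 30; total 60.
- Exact t-test: 30.1 per arm; power with 30 per arm is 89.9%.

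The figure of 60 reproduces, so there is no error in that arithmetic. The abstract says "Sixty patients with respiratory disease due to documented sulfur mustard gas exposure will be randomized", so the number randomised equals the number that must complete. Equal arms of 30 are assumed from the two-arm design and blocks of four.

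**3. Possible overstatement from one-sided removal.** Assumptions, none of them given in the documents: k of 30 rehabilitation patients are removed before week 6, their true mean change would have been m, those who stay average 105 s, and no control is removed. Then:

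- Analysis after removals: 105 − 20 = 85 s.
- All randomised: [(30 − k) × 105 + k × m] / 30 − 20.
- Overstatement: k × (105 − m) / 30.

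| k | m = 0 s: all-randomised difference | Overstatement | m = −50 s: all-randomised difference | Overstatement |
|---|---|---|---|---|
| 2 | 78 s | 7 s (8% of 85 s) | 74.7 s | 10.3 s (12%) |
| 4 | 71 s | 14 s (16%) | 64.3 s | 20.7 s (24%) |
| 6 | 64 s | 21 s (25%) | 54.0 s | 31.0 s (36%) |

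**4. The other end of the range.** If removals are balanced and unrelated to outcome, each arm's expected mean is unchanged and the difference stays at 105 − 20 = 85 s, so the bias is zero. Only precision is lost. With an assumed 5%, 10%, 15% or 20% lost from both arms, power falls from 90.9% to 89.4%, 87.8%, 85.9% or 83.8% (normal approximation).

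**The case against.** The strongest reply is that the article promises intention to treat in plain words, that exclusion may mean only the end of active participation, and that nothing says data already collected are thrown away. Handling of missing outcomes may sit in an analysis plan that is not shown. A reader might infer that intention to treat cannot be delivered at all. The documents do not support that: anyone excluded after week 6 can already have the primary outcome, and only exclusions in roughly the first 6 of 52 weeks can cost it.

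A reader might also infer that such problems come to light only in the rehabilitation arm. That goes too far. Controls have monthly visits and undergo the same cycle, muscle and walking tests. The illness trigger refers to continuing in the study, which applies to both arms, and malignancy and cognitive or psychiatric disease have no link to the programme. An imbalance is plausible but not shown.

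Nor do the documents support saying that the effect is biased. They give no number of exclusions, no split by arm and no outcomes of those excluded; they do not even say that anyone has been excluded. Death, emigration and withdrawal are unavoidable losses that need handling, not improper removals. Exacerbations and hospitalisations rest partly on clinical records, so an undercount is possible but not inevitable.

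What stands after all this is the stated rule. It removes patients from the study for reasons of health, the next sentence promises the opposite in analysis, and no text reconciles them.

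**Conclusion.** The contradiction is real and lies in what the article states, not in what it leaves to another document. As written, the rule would lose outcomes for health-related reasons and puts the main comparison at risk of bias, with a plausible direction in favour of rehabilitation.

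The size is unknown. The illustration of 7 to 21 s out of 85 s rests on 2 to 6 removals, all before week 6, all in the rehabilitation arm, and all among patients with no gain; a change of −50 s in those patients would raise it to 10 to 31 s. With balanced removals unrelated to outcome it is zero. These figures show why the wording matters and are not an estimate of what has happened.

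**What to change.** Reconcile the two statements in Recruitment and consent:

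- Say that leaving the rehabilitation programme is not leaving the study. When sessions stop remains a clinical decision that this change does not touch.
- Say that only withdrawal of consent for data collection, emigration or death ends follow-up.
- Seek the outstanding 12-month assessments, and exacerbations and hospitalisations from records, for all randomised patients where consent allows. Use any 6-week data already collected.
- Analyse every randomised patient in the allocated arm.
- Report exclusions and deaths by arm, with their timing relative to week 6.
- Add a sensitivity analysis for missing 6-week outcomes, for example assigning no gain. That value is itself an assumption and should be labelled so. The analysis is needed because enrolment ended in August 2018 and the article appeared in February 2019, so missed 6-week tests cannot now be recovered.

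The cost is one amended paragraph, limited extra follow-up and one additional analysis. The effect estimate may turn out smaller. Patients unfit to cycle may still lack an endurance measurement, so the change reduces the risk of bias without removing it.

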## Discussion

This study using a controlled randomized clinical trial will investigate the impact of a PR programme on people with mustard gas lung disease. If the programme proves efficacious, pulmonary rehabilitation centres can be established and expanded across the country/countries that have been victims of chemical attacks.

Among the limitations of this study are the following: participation in the rehabilitation centre exercises for 6 weeks, three times a week might be difficult for those participants who are employed; and the length of the project (being 1 year long) raises the risk of participant drop-out.

Some of the strengths of this study are as follows: this is the first PR protocol that is being conducted for sulfur mustard victims; the emphasis on the use of objective and safe methods in assessing patients, instead of subjective methods, is an additional strength of this study; and the results of this study can be used in other regions that have also been victims of mustard gas exposure.

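### The per-protocol analysis selects on attendance in the PR arm only and is unranked beside ITT; its contrast can be biased either way, and a randomisation-based attendance estimate would serve better

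*Protocol article*

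**What the plan says.** Under Recruitment and consent, the protocol article fixes a compliance rule and names two analyses in one sentence: "Compliance with PR is defined as missing fewer than four sessions and a per-protocol analysis as well as intention to treat" will be carried out. It does not spell out that compliance defines the per-protocol set, but the sentence has no other natural reading.

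The number of sessions is not printed as a total. It follows from the limitation in the Discussion: "participation in the rehabilitation centre exercises for 6 weeks, three times a week might be difficult for those participants who are employed". Under Interventions, only the intervention group receives PR; controls continue usual medication with advice on activity.

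The section Sample size and statistical analysis gives a single significance level of 0.05 and a comparison adjusted for baseline. It names no analysis set. No section ranks ITT against per-protocol.

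**The concern.** An attendance rule has no counterpart among patients who have no sessions to attend. Applied as written, it keeps a subset of the PR arm, chosen on behaviour after randomisation, and has no matching filter for controls. If attendance is related to how a patient would have changed over 6 weeks anyway, the two groups differ for reasons other than treatment, and the contrast is not centred on zero when PR does nothing.

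Ranking the analyses later would settle which one counts. It would not repair the per-protocol estimate. Until they are ranked, two tests of the same question stand side by side at 0.05, and nothing in the article prevents a positive per-protocol result from being put forward when ITT is negative.

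**Working it through.** **The plan's own figure.** The inputs are "Assuming a 105-s improvement in the time limit in the treatment arm", "a 20-s improvement in controls with an SD of 100", 90% power and a 5% level. Two-sided testing and equal arms are assumed. The difference is 105 - 20 = 85 s. Per arm, n = 2 x (1.960 + 1.282)² x 100² / 85² = 29.1, so 30, or 60 in total. The stated 60 is reproduced; power by noncentral t with 30 per arm is 89.9%.

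**The rule.** 6 x 3 = 18 sessions. Missing at most 3 means attending at least 15, or 83%.

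**Bias with no true effect.** Let c be the compliant share of the PR arm and g the gap between compliers and non-compliers in mean baseline-adjusted six-week change without any treatment effect. The whole PR arm has mean c x (compliers) + (1 - c) x (non-compliers), and randomisation makes the control mean equal to this in expectation. So compliers minus controls = (1 - c) x g.

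The documents give neither c nor g. Assumed ranges: c = 60-80%, g = 25-75 s in size. Also assumed: no controls are removed, and the SD stays at 100 s. The standard error is 100 x √(1/n₁ + 1/30), with n₁ = 30c: 29.8 s (18 patients), 28.5 s (21) and 27.4 s (24). Rejection is two-sided at 5%, by noncentral t.

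| Gap g | c = 60% (18 v 30) | c = 70% (21 v 30) | c = 80% (24 v 30) |
|---|---|---|---|
| 25 s | 10 s; 6.2% | 7.5 s; 5.8% | 5 s; 5.4% |
| 50 s | 20 s; 10.1% | 15 s; 8.1% | 10 s; 6.5% |
| 75 s | 30 s; 16.6% | 22.5 s; 12.1% | 15 s; 8.4% |

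The bias of 5-30 s is 6-35% of 85 s (5/85 and 30/85). If g is negative the sizes and two-sided rates are the same but the bias runs against PR: at the extreme, a true 85 s would appear as 85 - 30 = 55 s.

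**Second model as a check.** Let attendance be a latent variable with correlation ρ to the outcome, and cut the PR arm at its compliant share. The bias is ρ x 100 x φ(k)/c, where φ is the standard normal density and k the normal cut-off that leaves a share c above it. For ρ from 0.1 to 0.5 (assumed) it is 3.5-17.5 s at 80% compliance and 6.4-32.2 s at 60%, a similar range.

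**Cost of leaving the two unranked.** In 40,000 simulated trials per setting with no true effect, the chance that at least one of ITT and per-protocol is significant was as follows.

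| Compliance | ρ = 0 | ρ = 0.3 | ρ = 0.5 |
|---|---|---|---|
| 80% | 6.3% | 8.5% | 11.6% |
| 70% | 7.1% | 10.3% | 16.4% |

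The ρ = 0 column is multiplicity alone, with no selection.

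**Which exposure to use in a randomisation-based estimate.** Suppose full attenders gain 85 s and non-compliers half of that, 42.5 s (assumed). Dividing the ITT effect by c, as a yes/no 15-session exposure does, gives:
- c = 80%: (0.8 x 85 + 0.2 x 42.5) / 0.8 = 76.5 / 0.8 = 96 s
- c = 70%: 72.25 / 0.7 = 103 s
- c = 60%: 68 / 0.6 = 113 s

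The yes/no version therefore overstates 85 s by 11-28 s if partial attendance helps. It is still centred on zero when PR has no effect at any dose, which the per-protocol contrast is not.

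**The case against.** The strongest reply is that ITT is promised, that reporting per-protocol beside it is ordinary, and that the rank and the full definition of the set may stand in an SAP or full protocol not shown here. This holds against a complaint about the missing rank alone. It does not dispose of the point, because the article itself fixes a one-sided attendance rule for a between-arm analysis, and ranking would not make that estimate unbiased.

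Three stronger readings are tempting and are not supported:
- **That per-protocol will carry the conclusion.** No section says so. The most that can be said is that nothing in the article rules it out.
- **That attenders are fitter, so the bias favours PR.** The documents do not say this. Their only remark on attendance is that employed participants may find it difficult. If employed patients are the fitter ones, the rule would remove fitter PR patients and the bias would run against PR.
- **That the comparison is with every control.** The article does not define the per-protocol set for controls. The post-randomisation exclusions in the same section apply to both arms and could remove some. Only the attendance filter is one-sided by construction.

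On size, adjustment for baseline absorbs part of any fitness difference already present, so the relevant gap is the one that remains in adjusted change. A gap of 75 s is 0.75 SD and has no support in the documents; at 25 s the rejection rate is only 5.4-6.2%. The objection that a threshold-based complier estimate has its own bias also stands, and it decides the form of the fix.

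**Conclusion.** The point holds in a limited form. The attendance rule selects patients in one arm after randomisation, so the per-protocol contrast is not protected by randomisation and may be biased in either direction. The article leaves it unranked beside ITT.

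Under the assumed 60-80% compliance and 25-75 s gap, the bias is about 5-30 s and two-sided null rejection about 5.4-17%. That can matter for a borderline result, but the bias could not produce the planned 85 s by itself. Both inputs are assumptions and the sign is unknown. The ITT comparison and the sample size of 60 are unaffected by this point. It is a modest, cheaply corrected weakness in how the compliance analysis is specified.

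**What to change.** 1. State that ITT alone decides the primary question and that any per-protocol result is supportive. Define the per-protocol set for both arms.
2. For the effect of attendance, report a randomisation-based estimate instead of, or beside, the naive per-protocol contrast: two-stage least squares with randomised arm as instrument, number of sessions attended as the main exposure (zero for controls), and baseline endurance time as covariate.
3. Give the 15-of-18 threshold version only as a sensitivity analysis. Say that it assumes fewer than 15 sessions have no effect, and that it overstates the effect if they do.

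The cost is a few sentences and one extra model, using attendance records that the compliance rule already requires; N stays at 60. The downsides are a wider interval than the naive contrast gives and, for the sessions model, an assumed linear dose-response. Both ITT and the new model need six-week outcomes from PR patients who attended poorly. Trial status puts the end of enrolment in August 2018, so six-week data should already have been collected when the article appeared in February 2019. The ranking should therefore be dated and recorded before the arms are compared.

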### Follow-up

The participants of both groups will be visited 12 times, at 1-month intervals (Fig. 1). At the ‘zero visit’, all individuals who are most likely eligible (based on their medical records) to enrol in the study will be invited. The participants will then be carefully examined by specialists and assessed for presenting the inclusion or exclusion criteria.

### Data management

Patient data will be collected from their medical records, questionnaires completed by the questioner, test reports, documented physician comments, researchers’ observations and patient interview. A technician will enter the data from the ‘Case Report Form’ (CRF) into SPSS statistical software. To ensure the accuracy of data entry, double data entry will take place at every stage of data gathering.

The Coordinating Team, Steering Committee, Endpoint Adjudication Committee, Data Management Team and Data Monitoring Committee are responsible for the implementation, control and monitoring of the correct implementation of the study.

### Sample size and statistical analysis

Assuming a 105-s improvement in the time limit in the treatment arm and a 20-s improvement in controls with an SD of 100, 90% power and a significance level of 5% requires 60 patients to complete the study.

The data will be cleaned and assessed for outliers and missing variables. Outcomes will be compared using ANOVA adjusted for baseline parameters. The data will be analysed by *t* test, chi-square test and, if required, non-parametric tests and with Excel 2010 and SPSS Statistics 20 software at a level of significance of 0.05.

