### Outcomes

#### Outcome assessment

Before starting the outcome assessment, assessors will be trained in and familiar with the assessment protocol and instruments. They will be blind to the study participants’ group allocations. Outcomes will be measured at baseline prior to the intervention, after 6 weeks and after 12 months from study entry.

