#### Primary outcome

The primary outcome of the study will be the cycle endurance time at 70% of baseline workload, measured at the end of 6 weeks. An increase of > 105 s in the endurance time has been defined as the minimum clinically important difference and will be used as a threshold for responder analysis [29].

A symptom-limited incremental exercise test (IET) will be used to determine the W_max_ of each participant at baseline. After 3 min of acclimatization and 1 min of unloaded cycling, the workload is increased by 10 W/min until the patient can no longer bear heavier loads. The highest workload that each individual can complete during 60 s of pedalling will be defined as the W_max_ [30]. A practice constant work rate test will be performed approximately 1 h after the IET at 70% maximum workload. Three minutes of unloaded cycling (0 W) will be given to allow for respiratory adaptation and warm up [31]. At the next session, a few days later, the constant workload test will be repeated and the outcome of this taken as the baseline measure of the endurance time [30].

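### As written and without imputation, the 12-month comparisons use completers only and ignore the 6-week results of patients lost later; a mixed model would use them

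*Protocol article*

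**What the plan says.** The Sample size and statistical analysis section of the protocol article states: "Outcomes will be compared using ANOVA adjusted for baseline parameters". It continues: "The data will be analysed by *t* test, chi-square test and, if required, non-parametric tests". On missing data it says only: "The data will be cleaned and assessed for outliers and missing variables". No repeated-measures model and no imputation is named.

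The schedule is in Outcome assessment: "Outcomes will be measured at baseline prior to the intervention, after 6 weeks and after 12 months from study entry". The primary outcome is the "cycle endurance time at 70% of baseline workload, measured at the end of 6 weeks", so every 12-month comparison is secondary.

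Recruitment and consent promises that "a per-protocol analysis as well as intention to treat will be carried out". The same section begins a list with "During the study, the patient will be excluded from the study if any of the following occurs"; the grounds include withdrawal, intervening illness, emigration and death. The Discussion gives as a limitation that "the length of the project (being 1 year long) raises the risk of participant drop-out".

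**The concern.** Each named method needs an observed outcome for every patient it includes. Applied at 12 months to the data as observed, it compares only patients who reached that visit. A patient assessed at 6 weeks and lost later contributes nothing, although the 6-week value is the best available information on the missing one.

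The article itself gives reasons to expect such patients: a year of follow-up, a stated drop-out risk and a list of grounds for leaving the study. Only one arm attends sessions three times a week for 6 weeks, so loss need not be balanced or unrelated to response. At stake is the durability result, that is, whether any benefit at 6 weeks is still present at 12 months.

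**Working it through.** **The plan's own figure.** Inputs from Sample size and statistical analysis: difference 105 - 20 = 85 s, SD 100 s, power 90%, significance level 5%. With 1:1 allocation and a two-sided test, n per arm = 2 × (1.960 + 1.282)² × 100² / 85² = 29.1, so 30 per arm and 60 in total. The stated 60 reproduces. It is used here only to set the scale.

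**Where the bias comes from.** Let b be the slope of the 12-month value on the 6-week value given baseline, and m the mean 6-week residual among patients retained in an arm. The completers' contrast is then off by approximately

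bias ≈ b × (m in the rehabilitation arm - m in controls).

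This is zero if loss is random, if it depends only on the adjusted baseline, or if it selects equally in both arms.

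**Simulation in seconds.** Assumed: 30 per arm, true 12-month difference 85 s, SD 100 s, correlation 0.6 between 6-week and 12-month changes, baseline unrelated to change, 4000 trials per row (simulation error about 0.5 s).

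| Assumed loss | Lost | Completers' ANCOVA | Analysis also using the 6-week value |
|---|---|---|---|
| Completely random | 20% | 85.2 s | 85.2 s |
| Depends on baseline only | 30% | 85.0 s | 85.2 s |
| Poor 6-week response, rehabilitation arm only; 10% random in controls | 20% | 104.7 s | 85.3 s |
| Poor 6-week response, same rule in both arms | 30% | 73.8 s | 85.0 s |

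The errors are 104.7 - 85 = +19.7 s and 73.8 - 85 = -11.2 s. Here b = 0.6, so the implied selection is 19.7 / 0.6 = 33 s and -11.2 / 0.6 = -19 s on the 6-week scale. The second is negative because controls improve less, so a common rule removes more of them and leaves a more favourably selected remainder.

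**Simulation in SD units.** Assumed: 30 per arm, true effect 0.5 SD, about 25% lost, baseline correlated 0.6 with 6 weeks and 0.5 with 12 months, and 6-week/12-month correlation r. Loss depends on the 6-week result in the rehabilitation arm only, with log-odds of about 1.5 per SD.

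| r | b = (r - 0.6 × 0.5) / (1 - 0.6²) | Completers' bias | Bias / b |
|---|---|---|---|
| 0.6 | 0.30 / 0.64 = 0.47 | +0.09 SD | 0.19 |
| 0.7 | 0.40 / 0.64 = 0.63 | +0.12 SD | 0.19 |
| 0.8 | 0.50 / 0.64 = 0.78 | +0.14 SD | 0.18 |

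The near-constant last column shows that the formula accounts for the results. From weak to steep dependence the bias runs from about +0.03 to +0.18 SD. With the same rule in both arms it is -0.04 to -0.06 SD. The joint analysis stays within about 0.01 SD in these cases, and its standard error is 1-8% smaller (for example about 0.25 against 0.26). The seconds example gives somewhat larger errors (+0.20 and -0.11 SD) because its baseline explains none of the later change and its assumed effect is larger.

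**Loss driven by the 12-month state itself.** Here the joint analysis is biased too, but less: 0.14 to 0.22 SD against 0.26 to 0.27 SD for completers' ANCOVA.

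**The case against.** The strongest reply is that the article never says that patients without a 12-month value are dropped. A reader might infer this from the word ANOVA, but ANOVA does not exclude prior imputation, and the handling of missing values may be set out in an analysis plan or full protocol that is not shown. That stands. The absence of a missing-data rule is not the point here; the point is the choice of the methods that are named.

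Second, the intention-to-treat promise follows directly on the definition of compliance, so it contrasts analysis as randomised with analysis by attendance and does not address missing outcomes. That also stands in part: the tension with a completers' analysis is real but is not a literal contradiction. Nor is the mixed model full intention to treat by itself, since it omits patients with no follow-up value.

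Third, size and direction rest on assumptions. The +0.14 SD figure needs steep dependence (log-odds 1.5 per SD, about a 4.5-fold change in odds). At log-odds 0.5 and 25% loss the bias is about 0.03 to 0.07 SD. At 10% loss with log-odds 0.5 to 1.0 it is 0.02 to 0.04 SD, against a standard error of about 0.24. When loss depends on each patient's deviation from the arm's own 6-week mean, equally in both arms, there is none. It is tempting to conclude that the plan favours rehabilitation at 12 months; the documents give no drop-out rate or mechanism and do not support that.

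Fourth, the near-zero bias of the joint analysis is partly built in, because loss was generated from the observed 6-week value. The last simulation shows the limit of this: bias is reduced, not removed.

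**Conclusion.** The point holds as a cheap improvement to the secondary 12-month comparisons. Without imputation, the named methods give completers' contrasts that ignore known 6-week results, in a trial that expects drop-out. The possible bias is modest: about +0.03 to +0.18 SD if loss follows the 6-week response in the rehabilitation arm only, about -0.05 SD if it does so in both arms, and none if loss is random or depends only on baseline. Against a standard error of about 0.26 SD, the upper value is 0.18 / 0.26 = 0.7 standard errors. All these figures rest on assumed loss rates, mechanisms and correlations.

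A reader might extend the point to the primary analysis. Nothing here shows a defect in it: it is at 6 weeks, there is no earlier follow-up value to borrow from, and baseline-adjusted ANOVA is a standard choice for two arms.

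**What to change.** In Sample size and statistical analysis, state that the 12-month contrast of each repeatedly measured continuous outcome is estimated from a linear mixed model with:

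- the 6-week and 12-month values as outcomes;
- the baseline value as covariate;
- arm, visit and arm-by-visit as fixed effects;
- an unstructured covariance between visits;
- all randomised patients with at least one follow-up value, in the arm to which they were randomised.

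Keep the per-visit baseline-adjusted ANOVA as a sensitivity analysis at 12 months. It may stay as the 6-week primary analysis.

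The cost is a change of wording and a few lines of syntax in SPSS, which the article already names. No new data or visits are needed. The model assumes that missingness is explained by observed values, a weaker assumption than the completers' ANOVA makes. It reduces but does not remove bias from unobserved later deterioration, and it does not recover patients lost before week 6. The text should say so.
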